**Fig. 2 Fig2:**
[figure not shown]
Trial flow diagram

### Informed consent

Study coordinators will approach potential participants in-person or via telephone to discuss the study goals, risks, and alternatives, and obtain oral and written informed consent. Participants will identify a caregiver and a separate informed consent will be obtained.

### Additional consent provisions for collection and use of participant data and biological specimens

There are no additional consent provisions for this study.

### Intervention description

#### Intervention group – DeCIDE PC intervention

Participants in the intervention group will receive the DeCIDE PC intervention in addition to standard of care. Following study enrollment, participants randomized to the DeCIDE PC intervention group will be connected with the CHW at their enrollment site. The CHWs will then meet with the patient-caregiver dyad or the patient alone to perform a baseline assessment of their SDOH and barriers to healthcare. Following the baseline assessment, CHWs will perform weekly check-ins and tailor ongoing support to the individual needs of the patient and caregiver. CHWs will have access to the electronic medical record (EMR) at their respective sites to follow their patients’ course of care and communicate with the clinical team through patient notes and direct messaging. The CHW intervention activities will include educating patients on palliative and hospice care, facilitating palliative and hospice care referrals and care team communications, linking patients to community-based resources, empowering patients to discuss their goals of care with their oncologists and encouraging patients to discuss advance care planning with their caregivers and families, removing barriers to care by addressing SDOH, and providing instrumental, logistical, and emotional support [21, 23, 24]. This intervention will be refined based on the findings from Aim 1, which will include input from patients and caregivers, stakeholders, the CAB, and the baseline environmental scan.

We will hire and train one CHW at each enrollment site in the first year of the study. All CHWs will undergo a three-month CHW training program, which will include a combination of synchronous (didactic and problem-based sessions, communication and motivational interviewing skills training), asynchronous, and experiential training components. For the purposes of program evaluation, all CHWs will complete pre- and post-training tests to assess knowledge gain, perceived competence, and satisfaction with the training. CHWs will also undergo longitudinal training throughout the study period. We will also onboard a Palliative Care Liaison at each enrollment site, who will be a member of the palliative care team and will serve as a resource and source of support for the CHW throughout the study. Finally, CHWs will have access to up-to-date palliative care content from national organizations, such as the Center to Advance Palliative Care (CAPC).

### Choice of comparator

#### Comparator group – enhanced standard of care

Participants in the comparison group will receive standard of care in accordance with national and local guidelines for management of their disease. Due to the many known benefits of palliative care for patients with advanced cancer, a brochure on palliative care and its service offerings will also be provided to patients within the enhanced standard of care pathway at the time of enrollment. Additionally, patients may be referred to specialty palliative care at any time throughout the study period at their oncologist’s discretion.

### Criteria for discontinuing or modifying allocated interventions

We will discontinue the study intervention at the participant’s request.

### Strategies to improve adherence to interventions

To improve adherence to the intervention and survey completion, participants in each dyad will receive monetary compensation ($50 per participant, $100 per dyad) upon completion of the 6-month survey. If the patient passes away prior to administration of the 6-month survey, the patient’s caregiver or family will receive the monetary compensation.

### Relevant concomitant care permitted or prohibited during the trial

Patients will be permitted to receive oncologic care throughout the trial. Oncologists may refer patients in the enhanced standard of care group to speciality palliative care, however, to prevent crossover between groups throughout the trial, cannot refer patients to CHW support. Participants will be prohibited from participating in concomitant clinical trials in palliative care.

### Provisions for post-trial care

We do not anticipate that participants will suffer harm from trial participation, and therefore do not anticipate the need for additional compensation or ancillary care. Patients will continue to receive oncological standard of care following study completion.

### Outcomes

The primary, secondary, and exploratory outcomes are summarized in Table 3. The primary outcome for this study is ACP, defined as a self-reported or documented Advance Directive, such as a living will (LW) or durable power of attorney (DPOA), or a documented discussion of care preferences between the patient and caregiver or the patient and the healthcare team. ACP has been widely used and validated in palliative care studies [25, 26]. Our principal secondary outcome is QOL, measured by the Functional Assessment of Chronic Illness Therapy - Palliative Care (FACIT-Pal) [27]. FACIT-Pal contains five subscales, including physical, social/family, emotional, and functional wellbeing, as well as palliative care. Participants will be provided with a list of statements and asked to rate each statement on a scale of 0 (not at all) to 4 (very much) based on their recollection of the last 7 days. The subscale scores will then be added to generate a total score, with higher scores reflecting a higher QOL. FACIT-Pal has also undergone extensive validation in palliative care studies [27, 28]. Other secondary outcomes include (1) Quality of Communication (QOC), measured by the QOC Questionnaire [29]; (2) hospice care utilization within 14 days of death; and (3) patient symptoms, measured by the Edmonton Symptom Assessment Scale (ESAS) [30] and the Center for Epidemiologic Studies Depression Scale (CES-D) [31].

**Table 3 Tab3:** Overview of primary, secondary, and exploratory outcome measures

Outcome measure	Description
**Primary outcome**	
Advance care planning	Defined as a self-reported or documented Advance Directive, such as a living will (LW) or durable power of attorney (DPOA), or a documented discussion of care preferences between the patient and caregiver or healthcare team
**Secondary outcomes**	
Quality of life	Functional Assessment of Chronic Illness Therapy - Palliative Care (FACIT-Pal) [27]
Quality of communication	Quality of Communication (QOC) Questionnaire [29]
Hospice care utilization	Utilization of hospice care within 14 days of death (Yes/No)
Patient symptoms	Edmonton Symptom Assessment Scale (ESAS) [30] Center for Epidemiologic Studies Depression Scale (CES-D) [31]
**Exploratory outcomes**	
Patient physician communication	Princess Margaret Hospital Satisfaction with Doctor Questionnaire (PMH/PSQ-MD) [32, 33]
Caregiver satisfaction	Family Satisfaction with Advanced Cancer Care (FAMCARE) [34]
Palliative and hospice care utilization	Palliative care consulted (Yes/No), hospice care referral made (Yes/No), length of stay in hospice care (days), hospice care withdrawal (Yes/No)
Resource utilization	Length of stay in hospital (days), length of stay in the Intensive Care Unit (days), visits to the Emergency Department (number of visits), readmission(s) (Yes/No), timing of readmissions (days since discharge), time spent with CHW (hours), cost (dollars)
Social determinants of health	Protocol for Responding to & Assessing Patients' Assets, Risks, & Experiences (PRAPARE) [35]

### Participant timeline

The timetable for data collection is presented in Table 4. Research coordinators from each enrollment site will screen potential participants for eligibility, obtain informed consent, enroll patients and their caregivers, and perform random allocation. They will then conduct EMR review and administer surveys at baseline (t_0_), 2 months (t_1_), and 6 months (t_2_).

**Table 4 Tab4:** Timetable for data collection

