### Allocation

Patient-caregiver dyads will be randomized in a 1:1 ratio into one of two groups, the DeCIDE PC intervention group or the enhanced standard of care group. To yield balanced groups, the random allocation sequence will be computer-generated with a block size of 6. Randomization will be stratified by cancer stage (AJCC stage III or IV). Allocation will be entered into the Research Electronic Data Capture (REDCap) database by a unblinded statistician at the central study site who is not directly involved in the study design, study conduct, or participant enrollment. Randomization will be performed immediately after enrollment by unblinded research coordinators through REDCap.

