### Blinding

The principal investigators and lead statistician will be blinded to participant randomization. Due to the nature of the intervention, trial participants and oncologists will not be blinded. Additionally, the research coordinators and program manager will not be blinded to treatment allocation. We do not anticipate the need for unblinding, however, any inadvertent unblinding will be reported.

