### Data collection

Data collection will be the responsibility of the research coordinators with oversight from the site principal investigators. Investigators will be responsible for ensuring the accuracy, completeness, legibility, and timeliness of the data collection.

Baseline demographics, medical history, performance status, and disease characteristics will be obtained from EMR review. The remaining data will be gathered from EMR review and surveys administered at baseline (within 1 week of enrollment), 2 months, and 6 months. Research coordinators will administer all surveys by telephone and record responses in the central REDCap database, stored on password protected computers on servers within Johns Hopkins University [37].

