### Plans to promote participant retention and complete follow-up

To promote participant retention and complete follow-up, research coordinators will make every effort to remain in contact with study participants throughout their time on the study. If a participant is not reachable within 2 weeks of the baseline, 2-month, and 6-month surveys, the research coordinators will attempt to regain contact through three telephone calls, scheduled visits for clinical care, and if necessary, a letter to the participant’s last known mailing address. These attempts will be documented in the participant’s medical record and study file. If issues with retention occur, these will be brought to the CABs to aid in addressing and correcting these issues.

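### Baseline surveys are scheduled after randomisation, by unblinded staff with unblinded patients, so self-reported t0 values are not protected from the allocation

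*Protocol article*

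**What the plan says.** Four sections of the protocol article fix the order of events.

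- **Participant timeline.** Coordinators screen, consent and enrol, "and perform random allocation. They will then conduct EMR review and administer surveys at baseline". Table 4 has the same order, with the Allocation column ahead of Baseline (t0). Its t0 column includes ACP, FACIT-Pal, QOC, ESAS and CES-D.
- **Allocation.** "Randomization will be performed immediately after enrollment by unblinded research coordinators through REDCap".
- **Data collection.** The non-EMR data come partly from "surveys administered at baseline (within 1 week of enrollment), 2 months, and 6 months". On who conducts these, the section is equally plain: "Research coordinators will administer all surveys by telephone and record responses in the central REDCap database".
- **Plans to promote participant retention and complete follow-up.** Re-contact steps are given for the case "If a participant is not reachable within 2 weeks of the baseline, 2-month, and 6-month surveys", so some baselines may be later than one week.

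The Blinding section says that "trial participants and oncologists will not be blinded" and that "the research coordinators and program manager will not be blinded to treatment allocation". The intervention description says: "Following study enrollment, participants randomized to the DeCIDE PC intervention group will be connected with the CHW at their enrollment site". The CHW then makes an assessment of needs, followed by weekly check-ins. No section requires the t0 survey to be finished before allocation, before its disclosure, or before the first CHW contact.

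**The concern.** A baseline value is useful because allocation cannot have affected it. Here the survey scales and self-reported ACP are collected once both people on the telephone know the arm, and possibly after the CHW has begun work. Two things could move the answers: knowledge of the arm, and early intervention. Whether a patient answers the t0 survey at all could also depend on the arm.

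If such a value is then used as a baseline covariate, a change-score reference, an adjustment variable chosen for imbalance, or a predictor in an imputation, the analysis conditions on something that treatment may have altered. The analysis plan cannot repair this, because the pre-randomisation measurement would never have been taken.

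Quality of life matters most. It is the principal secondary outcome, and it sets the enrolment target: 80 per arm, against 70 for ACP.

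**Working it through.** **1. Sequence.** Consent and enrolment come first, then immediate randomisation, then the t0 survey on day d after enrolment. Here d runs from 0 to 7, and beyond 7 for patients who are hard to reach. The start of CHW contact has no stated date relative to d.

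**2. The plan's own figures (Sample size section).** Two-sided alpha is assumed, because the article does not state sidedness.

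- ACP, 30% v 60%, power 90%: n = [1.960·√(2·0.45·0.55) + 1.282·√(0.3·0.7 + 0.6·0.4)]² / 0.30² = (1.379 + 0.860)² / 0.09 ≈ 55.7, so 56 per arm; 56/0.8 = 70. Both agree with the article.
- QOL, SMD 0.5, power 80%: n = 2·(1.960 + 0.842)² / 0.5² ≈ 62.8, so 63 per arm (64 with the t distribution). Divided by 0.8 this gives 79 (80). It agrees with the article.

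The sample sizes are sound and are not affected by this point. They show that FACIT-Pal drives enrolment.

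**3. Where t0 can enter the stated analyses (Statistical analysis plan; Protocol non-adherence and missing data).**

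| Analysis | Use of t0 as stated | Exposed? |
|---|---|---|
| Primary ACP logistic model | Arm, site and stage; t0 ACP not named | Not as named |
| Rule adding covariates found unbalanced by arm | Not limited to pre-randomisation variables | Yes, if a t0 survey item is selected |
| Imputation, and MAR given earlier scores | Earlier scores inform missing ones | Yes, where t0 is used |
| QOL mixed model, random intercept | Role of t0 not stated | Depends on the model |
| Other longitudinal scales | Role of t0 not stated | Depends on the model |

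For QOL there are three cases. Let s be the t0 shift (intervention minus control, in SD units), r the correlation between t0 and 6 months, and 0.50 SD the true 6-month effect.

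- Free arm means at every visit, contrast at 6 months, complete data: estimate = 0.50, with no bias from s.
- t0 as covariate: estimate = 0.50 − r·s.
- Change from t0: estimate = 0.50 − s.

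**4. Illustration.** The documents give neither s nor r. Assume |s| from 0 to 0.10 and r from 0.5 to 0.7.

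| s | Adjusted, r = 0.5 | Adjusted, r = 0.7 | Change score |
|---|---|---|---|
| −0.10 | 0.55 | 0.57 | 0.60 |
| 0 | 0.50 | 0.50 | 0.50 |
| +0.10 | 0.45 | 0.43 | 0.40 |

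The movement is therefore 0 to 0.07 SD if adjusted and 0 to 0.10 SD as a change score, with either sign. For the attenuating end (s = +0.10) with 64 analysed per arm, power by the normal approximation is:

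- r = 0.5: from 81% to 62% (change score), or from 90% to 84% (adjusted).
- r = 0.7: from 96% to 83% (change score), or from 98% to 93% (adjusted).

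**The case against.** The strongest reply is that the primary comparison does not depend on t0 at all. That stands for the model as named. A reader might infer that a patient who completes a directive in week 1 because of the CHW is lost to the intervention arm as already having ACP. The article does not support this: t0 ACP is not a covariate, an exclusion or a change reference, and that patient still counts as having ACP at 6 months. Stage is a stratification factor, and the demographic and clinical baseline items come from the medical record, which allocation can hardly alter.

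Second, the QOL bias depends on a model detail that the article leaves open and that an analysis plan may settle. That also stands. A free-means model with a 6-month contrast largely escapes.

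Third, FACIT-Pal asks about the last 7 days, so a prompt survey mostly covers time before randomisation. This helps only in part. With a survey on day d, 7 − d days of the recall window precede randomisation, and on day 7 none does. Recall of earlier days can also be coloured by knowing the arm.

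Fourth, some tempting details go beyond the text. CHW check-ins are not shown to precede t0; their order is unspecified. Disappointment among controls is conjecture. The two-week rule does not mean that nothing is done before two weeks, since the same section commits coordinators to staying in contact throughout.

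None of these replies changes the order of events, which the article states outright.

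**Conclusion.** The sequence is a real weakness in a stated procedure: the t0 surveys come after allocation, with no blinding on either side and no hold on CHW contact. It bears mainly on FACIT-Pal and the other longitudinal scales, and only if t0 is used as a covariate or change reference. The primary ACP analysis is exposed only indirectly, through the imbalance-driven covariate rule or the imputation.

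The size cannot be derived from the documents. The range of 0 to 0.07 SD (adjusted) or 0 to 0.10 SD (change score) on a 0.50 SD effect rests wholly on the assumed shift and correlation. A reader might infer a fixed loss of 10 to 20% of the effect. That is not supported: the shift may be near zero after a week, and it may go either way. The case for acting is that the measurement cannot be recovered once a patient has been allocated, and that the change is cheap. Table 2 lists recruitment as pending, with first enrolment anticipated in September 2023.

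**What to change.** - Amend Participant timeline, Table 4, Allocation and Data collection so that the t0 surveys and the baseline ACP check are completed after consent and before allocation is performed or disclosed. Enforce this with a REDCap lock on the randomisation step.
- In the Statistical analysis plan section, limit covariate adjustment to variables measured before randomisation.
- If any patient has already been enrolled under the present order, record the dates of survey, allocation and first CHW contact, report them by arm, and add a 6-month QOL analysis without t0 adjustment.

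Cost: the sample size does not change. Allocation may come a few days after consent. Some patients may drop out before randomisation because they do not complete a telephone survey with several instruments. In a pragmatic trial in advanced cancer that loss should be counted and reported, but it falls before allocation and so cannot differ by arm.

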	**STUDY PERIOD**				
	**Enrollment**	**Allocation**	**Baseline (t**_**0**_**)**	**2 months (t**_**1**_**)**	**6 months (t**_**2**_**)**
**Eligibility screen**	X				
**Informed consent**	X				
**Allocation**		X			
**Demographic information**			X		
**Medical comorbidities**			X		
**Performance status**			X		
**Disease characteristics**			X		
**ACP**^**a**^			X	X	X
**FACIT-Pal**^**b**^			X	X	X
**QOC**^**c**^			X	X	X
**Hospice care utilization**			X	X	X
**ESAS**^**d**^			X	X	X
**CES-D**^**e**^			X	X	X
**PMH/PSQ-MD**^**f**^			X	X	X
**FAMCARE**^**g**^			X	X	X
**Palliative and hospice care utilization**			X	X	X
**Resource utilization**			X	X	X
**PRAPARE**^**h**^			X	X	X

^a^*ACP* Advance care planning

^b^*FACIT-Pal* Functional Assessment of Chronic Illness Therapy - Palliative Care [27]

^c^*QOC* Quality of Communication Questionnaire [29]

^d^*ESAS* Edmonton Symptom Assessment Scale [30]

^e^*CES-D* Center for Epidemiologic Studies Depression Scale [31]

^f^*PMH/PSQ-MD* Princess Margaret Hospital Satisfaction with Doctor Questionnaire [32, 33]

^g^*FAMCARE* Family Satisfaction with Advanced Cancer Care [34]

^h^*PRAPARE* Protocol for Responding to & Assessing Patients' Assets, Risks & Experiences [35]

### Sample size

We calculated our sample size to ensure sufficient power to detect a clinically meaningful difference in both our primary outcome (ACP) and our principal secondary outcome (QOL) between the study arms. With an alpha of 0.05 and power of 90%, we estimate a sample size of 56 participant per study arm to detect a 30 percentage point difference in ACP at 6 months, based on effect sizes from previous studies and conservatively assuming that 30% of patients in the enhanced standard care arm will have ACP [26, 36]. After accounting for a 20% attrition rate over the study period, the adjusted final sample size based on our primary outcome is 70 participants per study arm (140 participants total). The sample size calculation based on our principal secondary outcome of QOL, measured by FACIT-Pal, is based on a recent study, which found that palliative care was associated with a standardized mean difference (SMD) in QOL of 0.46 (95% CI 0.08–0.83) [28]. With an alpha of 0.05 and power of 80%, and after accounting for a 20% attrition rate, we estimate a sample size of 80 participants per study arm (160 participants total) to detect a SMD in QOL of 0.5. To ensure adequate power for both outcomes, we will plan to enroll 160 participants. We will seek to recruit a caregiver alongside each patient as a patient-caregiver dyad, but a lack of caregiver participation will not preclude a patient's enrollment. Our total potential sample size for the trial is therefore 320 participants, including 160 patients and 160 caregivers.

### Recruitment

The three enrollment sites have well established cancer centers, albeit different patient volumes. Based on the patient volumes at the three enrollment sites, we anticipate that 40% of the patient-caregiver dyads (65 dyads) will be recruited from Johns Hopkins Hospital, 35% (55 dyads) from University of Alabama at Birmingham Hospital, and the remaining 25% (40 dyads) from TidalHealth Peninsula Regional. Study recruitment will occur over 2–4 years. The CAB from each enrollment site will provide insight and advice to guide ongoing recruitment.

### Allocation

Patient-caregiver dyads will be randomized in a 1:1 ratio into one of two groups, the DeCIDE PC intervention group or the enhanced standard of care group. To yield balanced groups, the random allocation sequence will be computer-generated with a block size of 6. Randomization will be stratified by cancer stage (AJCC stage III or IV). Allocation will be entered into the Research Electronic Data Capture (REDCap) database by a unblinded statistician at the central study site who is not directly involved in the study design, study conduct, or participant enrollment. Randomization will be performed immediately after enrollment by unblinded research coordinators through REDCap.

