**Methods: Assignment of interventions (for controlled trials)**			
Allocation:			
Sequence generation	16a	Method of generating the allocation sequence (eg, computer-generated random numbers), and list of any factors for stratification. To reduce predictability of a random sequence, details of any planned restriction (eg, blocking) should be provided in a separate document that is unavailable to those who enrol participants or assign interventions	Yes
Allocation concealment mechanism	16b	Mechanism of implementing the allocation sequence (eg, central telephone; sequentially numbered, opaque, sealed envelopes), describing any steps to conceal the sequence until interventions are assigned	Yes
Implementation	16c	Who will generate the allocation sequence, who will enrol participants, and who will assign participants to interventions	Yes
Blinding (masking)	17a	Who will be blinded after assignment to interventions (eg, trial participants, care providers, outcome assessors, data analysts), and how	Yes
	17b	If blinded, circumstances under which unblinding is permissible, and procedure for revealing a participant’s allocated intervention during the trial	Yes

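### Randomisation is stratified by stage but not by site, and the single block size of 6 is published where the coordinators who enrol and allocate can read it

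*Protocol article*

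**What the plan says.** The Allocation section sets a 1:1 ratio and a sequence that is "computer-generated with a block size of 6. Randomization will be stratified by cancer stage". Its only stratification factor is AJCC stage, III or IV.

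The list is entered into REDCap by a statistician at the central site who has no part in design, conduct or enrolment. The next step belongs to site staff: "Randomization will be performed immediately after enrollment by unblinded research coordinators through REDCap". The Participant timeline gives the same role the earlier steps: "Research coordinators from each enrollment site will screen potential participants for eligibility, obtain informed consent, enroll patients and their caregivers, and perform random allocation".

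Site matters elsewhere in the article:
- Study setting says the three centres were picked because they differ in socioeconomic, cultural and demographic features.
- The intervention section says "We will hire and train one CHW at each enrollment site in the first year of the study", and patients are linked to their own site's worker.
- The Statistical analysis plan section puts site and stage in the logistic model for advance care planning (ACP). It names no covariates for quality of life (QOL) or the other secondary outcomes.

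The SPIRIT table, item 16a, says that "details of any planned restriction (eg, blocking) should be provided in a separate document that is unavailable to those who enrol participants". The item is marked as reported.

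Under Data management, site coordinators see only their own site's data, while the central study team sees all three sites.

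**The concern.** Site is a factor the trial treats as important, and it coincides with the person who delivers the intervention, at least at the start. Leaving it out of the stratification lets the arms drift apart within a site by chance. That would cost some precision in the site-adjusted comparison and make a CHW's caseload less even than planned.

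Separately, a fixed block of known size makes the end of each block predictable to anyone who can see the allocations in it. The people who decide whom to approach also see each allocation at their site. If they could foresee the next one, they could, knowingly or not, steer who is enrolled. Item 16a exists to prevent this, and printing the block size departs from it.

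**Working it through.** **Inputs.** Site sizes 65, 55 and 40 (Recruitment; sum 160). Ratio 1:1, blocks of 6, two stage strata (Allocation). The share of stage IV patients is not given, so I assumed 30%, 50% and 70%. Arrival order across sites is assumed random. The plan gives no figure of its own for balance or predictability, so there is none to reproduce.

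**Within-site balance, by hand.** Score allocations +1 and −1. Two allocations in the same block of 6 have covariance −1/5. A patient at a site with share p of the trial has about 5p block-mates from that site. The variance of the site's arm difference D is therefore about n(1 − 5p/5) = n(1 − p).

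| Site n | p | n(1−p) | SD of D | Chance that D is 8 or more in size (normal approximation) |
|---|---|---|---|---|
| 65 | 0.406 | 38.6 | 6.2 | D is odd, so 9 or more: 2[1−Φ(8/6.21)] ≈ 20% |
| 55 | 0.344 | 36.1 | 6.0 | D is odd, so 9 or more: 2[1−Φ(8/6.01)] ≈ 18% |
| 40 | 0.250 | 30.0 | 5.5 | D is even: 2[1−Φ(7/5.48)] ≈ 20% |

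**Simulation of the stated design** (8,000 runs at each stage share, with little change across shares):
- Arm difference of 8 or more: about 18–21% at each site, about 40% for at least one.
- A 60:40 split or worse: about 5–6% (n = 65), 9–10% (n = 55) and 19–20% (n = 40); about 28% for at least one site.
- With strata of site by stage and blocks of 6, the SD of D falls to about 1.5 and the chance of a 60:40 split to about 0.

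**Cost in efficiency.** Relative to perfect balance, the information in a site-adjusted comparison is Σ(n₁n₀/n)/(160/4). As n₁n₀ = (n² − D²)/4, this equals 1 − Σ(D²/n)/160. The expected value of D²/n is about 1 − p, and the three values of 1 − p sum to 2. The mean efficiency is thus 1 − 2/160 = 98.75%. Simulation gives a mean of about 98.7% and a 5th percentile of about 96%. Within the smallest site, a 24:16 split keeps 4 × 24 × 16/40² = 96%.

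**Predictability.** In a 3:3 block, the allocations that are certain are those in the closing run of one arm. Its expected length is 1 + 2/5 + (2/5)(1/4) = 1.5, so 1.5/6 = 25% are certain to someone who sees the whole stratum. The correct-guess rate below comes from guessing the arm that is behind:

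| Strata and blocks | What is seen | Correct guesses |
|---|---|---|
| Stage only, block 6 (as planned) | Own site | about 53% |
| Stage only, block 6 (as planned) | All sites | about 68% |
| Stage by site, block 6 | Own site | about 67% |
| Stage by site, blocks 4, 6 and 8 mixed | Own site | about 67% |

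**The case against.** Stratifying on a prognostic factor and adjusting for site in the model is an accepted design, and nothing in the Allocation section conflicts with the analysis section. Adjustment keeps chance imbalance by site out of the primary estimate, and the precision lost is slight. Concealment is also reasonable: a statistician outside enrolment loads the list, and REDCap releases each allocation only after enrolment. All of this stands.

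The two halves of the point also pull against each other. Because blocks run across three sites, a coordinator with an own-site view can predict little. Adding site strata would remove that protection.

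Three stronger readings are tempting but unsupported:
- **Allocation within a site is close to simple randomisation.** That would put the chance of an arm difference of 8 or more at 27%, 28% and 32% for sites of 40, 55 and 65. It ignores the balancing effect of shared blocks, which brings all three to about 20%.
- **Coordinators can foresee a quarter of allocations.** That needs sight of every allocation in the stratum, which Data management denies to site coordinators.
- **One CHW delivers the whole intervention at each site.** The article fixes one hire per site in the first year and does not rule out later ones. Even with perfect balance, caseloads differ (about 32, 27 and 20), and an arm difference of 8 shifts a caseload by only 4.

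The coordinators' role in collecting outcomes is a question of assessor blinding and adds no weight here.

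What remains is the departure from item 16a. That checklist wording is generic, but the article marks the item as met.

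**Conclusion.** The point holds as a cheap design improvement of low to moderate priority. It is not a threat to the validity of the primary comparison.

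Noticeable imbalance at one or more sites is fairly likely (about 40% for a difference of 8 or more, about 28% for 60:40 or worse), but it costs about 1.3% of efficiency on average and about 4% at the 5th percentile. As written, prediction by a coordinator with an own-site view is little better than chance. The realistic exposure is anyone at the central site who both recruits and sees all sites' data. The article makes this possible, since the coordinating centre is also the largest recruiting site, but it does not say that such a person exists.

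The figures rest on the planned site sizes, an assumed 30–70% share of stage IV, and random arrival order. If one site recruited alone for a period, its coordinators would in effect see the whole stratum, and predictability would move towards the 68% figure.

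**What to change.** Table 2 lists recruitment as pending. Before the first patient is enrolled:

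1. Replace the fixed block of 6 with randomly varying block sizes. The independent statistician should hold them in a document that enrolling staff cannot open, and the article should say only that block sizes vary and are withheld.
2. Add site to stage as a stratification factor only together with step 1. This gives six strata averaging 160/6, or about 27 patients.
3. Name site and stage as covariates in the QOL and other secondary models as well as the ACP model, unless the full analysis plan already does so.
4. State that nobody who enrols patients has access to other sites' allocations.

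The cost is a new REDCap allocation table and a paragraph of text. There are two downsides. A few blocks will be left incomplete. Under site strata, own-site guessing rises from about 53% to about 67%; varying the blocks removes certainty about where a block ends but does not lower that rate. If the team judges this a worse risk than chance imbalance by site, steps 1, 3 and 4 without step 2 are a defensible choice. Once enrolment has begun, changing the strata is no longer clean, but steps 3 and 4 remain open.
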